**Figure 1 Fig1:**
[figure not shown]
**Flow chart of the trial.** Participants with a diagnosis of primary dysmenorrhea will be recruited at the Third Teaching Hospital of Chengdu University of Traditional Chinese Medicine. All participants should endure a baseline period of three menstrual cycles and inappropriate participants will be excluded. A total of 222 participants will be randomized to three groups: treatment group A (treated before the menstruation), treatment group B (treated at the onset of menstruation), or control group C (waiting list group) in a 1:1:1 ratio. The trial period will consist of three baseline menstrual cycles, three menstrual cycles of treatment, and three menstrual cycles in the follow-up period, and the outcome will be measured at every visit.

**Table 2 Tab2:** **Study design schedule**

**Period**	**Baseline**	**Inclusion**	**Treatment**			**Follow-up**		
Visit		1	2	3	4	5	6	7
Menstrual cycle	−3 month	0 month	1 month	2 month	3 month	4 month	5 month	6 month
Patients		√						
Inclusion and exclusion criteria		√						
Informed consent		√						
Physical examination		√			√			
Medical history		√						
Comorbidities		√	√	√	√	√	√	√
Outcomes								
CMSS			√	√	√	√	√	√
VAS	√	√	√	√	√	√	√	√
RSS		√						
SDS and SAS		√			√			
Dysmenorrhea diary	√	√	√	√	√	√	√	√
PGF2a, PGE2		√			√			
Gynecological abdominal ultrasound B	√							
Trial evaluation								
Patient’s compliance					√			√
Reasons for dropout or withdrawals					√			√
Adverse events					√			
Safety evaluation								√

### Blinding

Double blinding of the clinician and patient is unfeasible owing to the unique nature of moxibustion operations. However, to ensure the integrity of the trial, the researchers will not assess the efficacy of treatment to avoid misleading the patients and inducing potential impacts on the compliance and outcome measurements. The therapist, the assessors of therapeutic effect, the data manager, and the statistician will be separated. Moreover, according to the principle of blinding, only patients allocated to the waiting list group will be told to wait for free treatments at the end of the study; allocation information will be strictly withheld from patients in the other two groups.

### Interventions

Acupuncturists must receive a license from the Ministry of Health of the People’s Republic of China and take an educational course to ensure their strict adherence to and familiarity with the study before they become eligible to treat patients in this study. Those participants allocated to a treatment group will be requested to attend (with their partner or support person if available) a training course and demonstration session by their tutors. The training course involves advice, demonstration of moxibustion, and instructions on how to do moxibustion safely at home. The woman or her partner or support person will be trained to light the moxibustion sticks and to hold an individual stick 2.5 to 3 cm above the two acupoints (SP6 and CV4). The participants will be told not to make the acupoints uncomfortable during treatment. They will be requested to perform this treatment for five to 10 minutes on each acupoint once a day for five to seven consecutive days, and will be supplied with sufficient moxibustion sticks to do so in each treatment period.

#### Rationale for selection of acupoints

The moxibustion treatment protocol to be used is consistent with the principles of traditional moxibustion theories. These principles state that the most common causes of dysmenorrhea in TCM are blood stagnation and cold-damp coagulation in the uterus. According to previous surveys and expert consultations, *Sanyinjiao* (SP6) and *Guanyuan* (CV4) are the most common acupoints used in PD treatment. SP6 is the convergent point of the spleen, liver, and kidney meridians according to TCM, and is closely related to the lower abdomen and uterus [27]. This makes SP6 one of the most commonly used points for gynecologic indications in clinical practice, especially for alleviating dysmenorrhea. The CV4 point in the conception vessel meridian is known as the root of vital *Qi*, and can exert a regulatory effect on the uterus because of its role of providing power to vital movement. Moxibustion at CV4 can treat dysmenorrhea because of its function of warming the conception vessel meridian, tonifying vital *Qi*, and promoting blood circulation to remove blood stasis.

#### Treatment group A (treated before menstruation)

Group A will be treated five days before expected menstrual onset and treatment will continue until menstruation begins. However, the subjects’ menstrual cycles may change and so the actual period of treatment will be five to seven days. The treatment will be the application of a moxa stick (herbal preparation with *Artemisia vulgaris*, Z32021062, Oriental Moxa Co., Suzhou, China) at acupoints SP6 and CV4 to patients in a supine position. The moxa roll is prepared by wrapping mugwort wool (herbal medicines may be mixed in it) with a piece of a paper. It is cylindrical, 1.5 cm in diameter, and 20 cm in length. A lighted moxa roll will be held 2.5 to 3 cm above the acupoint and moved upwards and downwards, to the left and right, or around. The patient should feel warmth but not scorching heat. Each point will be treated with moxibustion for five to 10 minutes.

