## Abstract

**Background:**

Dysmenorrhea is a common menstrual complaint among adolescent girls and women of reproductive age. The treatment of dysmenorrhea is typically selected from multidisciplinary options, including complementary and alternative medicine such as acupuncture and moxibustion. However, there are few published randomized controlled trials concerning moxibustion treatment for dysmenorrhea. This trial aims to investigate the efficacy and safety of moxibustion for primary dysmenorrhea, and to identify the optimal time of moxibustion treatment for primary dysmenorrhea.

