**Methods/Design:**

This protocol is for a randomized controlled trial in which the assessor and statistician will be blinded. A total of 222 eligible patients with dysmenorrhea will be randomly assigned to three groups in a 1:1:1 ratio as treatment group A (treated before menstruation onset), treatment group B (treated at the onset of menstruation), or control group C (waiting list group). The participants assigned to the treatment groups will receive suspended moxibustion treatment at *Sanyinjiao* (SP6) and *Guanyuan* (CV4), while the waiting list group will not receive moxibustion treatment until the completion of the study. The trial period will consist of three baseline menstrual cycles, three menstrual cycles of treatment, and three menstrual cycles in the follow-up period. The primary outcome will be measured by changes in the Cox Menstrual Symptom Scale and the secondary outcomes will be measured using the Visual Analogue Scale, Cox Retrospective Symptom Scale, diary entries, the Self-rating Depression Scale, and the Self-rating Anxiety Scale. The safety of moxibustion will be assessed at every visit.

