#### Treatment group B (treated within menstrual period)

Group B treatment will start as soon as menstruation onsets, continuing for five consecutive days. The selection of acupoints and the procedure will be exactly the same as described above for treatment group A.

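### The protocol gives conflicting course lengths and starting points for moxibustion, so group A and group B can differ in amount of treatment as well as in timing

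*Protocol article*

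**What the plan says.** Finding the best time of treatment is one of the trial's aims. The abstract's Background states it as "to identify the optimal time of moxibustion treatment for primary dysmenorrhea", and the main Background and the Discussion repeat it. Only the comparison of group A with group B can answer it.

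Four places in the protocol article describe the course:

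- *Interventions* (all treated women): "five to 10 minutes on each acupoint once a day for five to seven consecutive days".
- *Treatment group A*: "Group A will be treated five days before expected menstrual onset and treatment will continue until menstruation begins". The next sentence allows for changing cycles and says that "the actual period of treatment will be five to seven days".
- *Treatment group B*: "Group B treatment will start as soon as menstruation onsets, continuing for five consecutive days". The section adds: "The selection of acupoints and the procedure will be exactly the same as described above for treatment group A".
- *Discussion*, limitations paragraph: treatment starts between five and seven days ahead of menstruation, or when pain starts. Menstruation may arrive a day or two early or late, so its start is hard to predict, and this may affect the therapeutic effect.

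The abstract gives "three menstrual cycles of treatment" for each participant.

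**The concern.** A comparison of A with B answers a question about timing only if timing is the sole planned difference between the arms. Here the points and the technique are declared identical, but the number of treatment days is not clearly so. Randomisation does not remove a difference that is built into the regimens.

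If A did better than B after receiving more sessions, course length would be a competing explanation, and a statement about optimal time would claim more than the design supports. The ambiguity also has a practical side: staff and participants who follow different sections would deliver different courses, above all in group B.

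**Working it through.** **1. The texts side by side**

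| Section | Applies to | Start | Days per cycle |
|---|---|---|---|
| Interventions | A and B | not stated | 5 to 7 |
| Treatment group A | A | 5 days before expected onset | until onset; said to be 5 to 7 |
| Treatment group B | B | onset of menstruation | 5 |
| Discussion | A or B | 5 to 7 days before menstruation, or onset of pain | not stated |

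There are three disagreements:

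- Group B has five days in its own section and five to seven in Interventions.
- Group A starts at a fixed five days before expected onset in its own section and within a five-to-seven-day window in the Discussion.
- Group B starts with menstruation in its own section, whereas the Discussion ties the later start to pain.

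**2. Group A's rule against group A's range**

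With a start five days before expected onset and a stop at onset, days treated = 5 + (actual onset − expected onset). Put in the shift of up to two days either way that the Discussion mentions:

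- On time: 5 + 0 = 5
- One or two days late: 5 + 1 = 6; 5 + 2 = 7
- One or two days early: 5 − 1 = 4; 5 − 2 = 3

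The stated range of five to seven covers onset on time or late. It leaves out early onset, which the rule would turn into fewer than five days.

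**3. Sessions over the trial**

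The plan gives no total, so there is none to reproduce. Sessions = days per cycle × 3 cycles, once daily.

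- A, stated range: 5 × 3 = 15 to 7 × 3 = 21
- B, own section: 5 × 3 = 15
- Ratio A/B: 15/15 = 1.00 to 21/15 = 1.40, so 0% to 40% more in A
- A, if onset were two days early in every cycle: 3 × 3 = 9, which is fewer than B
- If the Interventions section governs B as well: 15 to 21 in both arms

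**4. What this could mean on the Cox Menstrual Symptom Scale (CMSS)**

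The Sample size section expects means of 1.7 (A), 1.9 (B) and 2.5 (waiting list).

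- Planned A–B difference: 1.9 − 1.7 = 0.20
- Planned benefit of B over waiting list: 2.5 − 1.9 = 0.60

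Assumption, for illustration only: benefit is proportional to daily sessions per cycle and timing has no effect. Then 0.60/5 = 0.12 per daily session, and the A–B difference due to amount alone is 0.12 × (A's mean days − 5).

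| A's mean days per cycle | Difference from amount alone | Share of planned 0.20 |
|---|---|---|
| 5 | 0 | 0% |
| 6 | 0.12 | 60% |
| 7 | 0.24 | 120% |

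A mean below five days would reverse the sign. No section gives a dose-response relation or the distribution of A's course lengths.

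**The case against.** The best defence is that the nominal course is five days in both arms: A starts five days ahead and B runs for five days. The extra days in A come from anchoring treatment to a predicted event, so they belong to the pre-menstrual strategy under test. If the Interventions section governs, both arms have the same range and most of the imbalance disappears. The Discussion already admits that onset is hard to predict. Session count is also a crude measure, since both arms allow five to 10 minutes per point, a twofold spread that exceeds the 40%.

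Much of this stands. A fixed five days in B rests on the group B section alone. It is reasonable to treat variable length as part of strategy A, but then the contrast is between two regimens and should be named so. The limitation in the Discussion concerns unpredictable onset and does not mention unequal amounts of treatment. The spread in minutes is allowed equally in both arms, so it does not in itself separate them.

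A reader might infer more: that A will receive more treatment than B, or that extra sessions would explain most of any advantage for A. The documents support neither. Early onset can leave A with fewer sessions, and the figures of 60% and 120% require a mean of six or seven days together with a linear dose-response that no section states. If B matched or beat A despite more sessions in A, the imbalance would not explain that result.

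That the Analysis section does not name session count among its covariates is no fault either. Its list is given by way of example, and a condensed article may leave such detail to the analysis plan.

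**Conclusion.** The inconsistency is real and rests on what the article states. Its four descriptions do not agree on course length or start, and group A's stopping rule does not fit its own range. On the arm-specific text, A versus B can mix timing with amount of treatment: 15 to 21 sessions against 15, or fewer than 15 in A when menstruation comes early.

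The direction and size of any resulting bias cannot be determined from the document. Within A's stated range the effect on CMSS runs from none to about the whole planned 0.20 (0.24 at the extreme), and only under an assumed linear relation. The comparison of either treated arm with the waiting list is not affected by this mix, so the efficacy aim stands apart from it. What is at stake is how the timing conclusion may be worded.

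**What to change.** - Reconcile the Interventions, group A, group B and Discussion texts on course length and start, including what applies in group A when menstruation comes early. The choice belongs to the clinical team.
- Unless the reconciled courses have the same length, state the A-versus-B aim and conclusion as a comparison of two regimens (timing plus course length) and not of timing alone.
- Report sessions delivered per cycle by arm, descriptively.
- Do not restrict A versus B to cycles with equal session counts. Group A's count depends on when menstruation arrives after randomisation, so the restriction would select on a post-randomisation variable and break the randomised comparison.

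The cost is a wording amendment and one descriptive table. The downside is a narrower conclusion about timing if the courses stay unequal.

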#### Treatment group B (treated within menstrual period)

Group B treatment will start as soon as menstruation onsets, continuing for five consecutive days. The selection of acupoints and the procedure will be exactly the same as described above for treatment group A.

#### Control group C (waiting list group)

Participants in this group will receive no moxibustion-related intervention while the trial is in process. The subjects in this group will be asked to maintain their normal lifestyle, including diet, exercise, and workload. At the end of the trial, if participants in group C would like to be treated with moxibustion, we will offer free moxibustion treatment five times monthly for three menstrual cycles.

### Outcome assessments

#### Primary outcome measurement

##### Cox Menstrual Symptom Scale (CMSS)

The CMSS has been widely used for integrally evaluating patients’ symptoms [28]. The scale consists of 17 items or symptoms. In the severity evaluation, each symptom is scored via five levels: a score of 0 denotes that the symptom is not noticeable; one denotes it as slightly bothersome; two denotes it as moderately bothersome; three denotes it as severely bothersome; and four denotes it as very severely bothersome. In the duration evaluation, each symptom is scored in five grades: a score of 0 denotes that the symptom did not occur; one denotes that it lasted less than three hours; two denotes that it lasted between three and seven hours; three denotes that it lasted an entire day; and four denotes that it lasted several days. The CMSS will be used in each of the three menstrual cycles of treatment and the three menstrual cycles during the follow-up period.

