### Procedure

An independent assessor will initially assess each potential participant according to the inclusion and exclusion criteria. After completing a screening test, participants will enter a baseline period of three months (three menstrual cycles) without moxibustion treatment, during which they will be asked to record menstrual pain and use of acute medication in a dysmenorrhea diary.

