#### Secondary outcome measurements

##### Visual Analogue Scale

The severity of menstrual pain will be measured with the VAS, a 100-mm horizontal line with endpoints from no pain on the far left to the worst possible pain on the far right. The VAS is scored by measuring in millimeters the distance from the side marked no pain to the edge of the mark made by the patient. Possible scores range from a minimum of 0 to a maximum of 100 mm, as participants will be asked to indicate a perception of pain intensity scored from one to 100. The VAS will be used during baseline measurements and during the first, second, third, fourth, fifth, and sixth menstrual cycle after inclusion.

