##### Cox Retrospective Symptom Scale

The Cox Retrospective Symptom Scale (RSS) is a measurement of menstrual symptoms that has been shown to have high reliability, validity, and sensitivity [29]. It gives two scores: a Total Frequency Ratings score (RSS COX1) and an Average Severity Ratings score (RSS COX2). Lower scores indicate better health. The RSS will be used before treatment to assess the baseline condition of the patient.

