#### Analysis

A statistician blinded to the whole trial process will perform the statistical analysis using the SAS statistical software package (Version 9.1, SAS Institute Inc.) in the Computer Integrated Manufacturing System. For the evaluation of curative effect in this trial, the per protocol set (PPS) will be used. The full analysis set (FAS) is determined according to an intention-to-treat population; all patients who are randomized and receive at least one treatment session will be included in the analysis set. The PPS is defined as the patients who complete the study and do not have major protocol violations. Demographic data and other basic indicators will be analyzed to test the balance of the three groups at baseline. The main indicators and global indicators will be analyzed within the FAS and PPS. The results will be described with the mean, standard deviation, median, P25 (Percentile 25), P75 (Percentile75), maximum, and minimum values of the differences between the treatment period and the baseline period. Between-group differences will be tested using repeated measure analyses of variance. The accepted level of significance for all analyses was *P* <0.05. Considering that the efficacy might be affected by factors such as age, age of menarche, and course of disease, all factors will be considered as co-variants for covariance analysis or logistic regression analysis when comparisons among groups are made. Missing data will be replaced according to the principle of multiple imputations.

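### The primary outcome is change in CMSS, but CMSS is scheduled only after randomisation, so the stated change from baseline cannot be computed

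*Protocol article*

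**What the plan says.** The abstract states: "The primary outcome will be measured by changes in the Cox Menstrual Symptom Scale". The Analysis section says that results will be described by summary statistics, specifically "values of the differences between the treatment period and the baseline period". It then names repeated-measures analysis of variance as the between-group test.

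The outcome section gives the CMSS schedule: "The CMSS will be used in each of the three menstrual cycles of treatment and the three menstrual cycles during the follow-up period". In Table 2 the CMSS row is empty under Baseline and under visit 1 (Inclusion), and ticked at visits 2 to 7.

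Other instruments are treated differently. For pain: "The VAS will be used during baseline measurements and during the first, second, third, fourth, fifth, and sixth menstrual cycle after inclusion". The diary has the same coverage. For the Cox Retrospective Symptom Scale (RSS): "The RSS will be used before treatment to assess the baseline condition of the patient". The abstract lists RSS among the secondary outcomes, and Table 2 ticks it at visit 1 only.

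**The concern.** A change from baseline needs a baseline value. The document states the CMSS schedule twice, in prose and in Table 2, and both leave out every time point before treatment. So the primary variable as worded and the measurement schedule contradict each other.

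Three things are at stake.

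- **Which variable is primary.** Unless the text is reconciled, someone will have to choose the primary variable after data have been collected.
- **Baseline comparability.** Balance between groups on the primary scale could not be shown.
- **Precision.** The trial has a three-cycle run-in before randomisation, but gains nothing from it on its primary scale. A baseline value cannot be collected prospectively once treatment has begun.

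RSS has a smaller, related fault. It is listed as an outcome but measured only before treatment, so it cannot show a treatment effect.

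**Working it through.** **1. Schedule, side by side (Table 2 and the outcome sections)**

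| Instrument | Baseline | Visit 1 | Visits 2–4 (treatment) | Visits 5–7 (follow-up) |
|---|---|---|---|---|
| CMSS (primary) | no | no | yes | yes |
| VAS | yes | yes | yes | yes |
| Diary | yes | yes | yes | yes |
| RSS | no | yes | no | no |

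CMSS has 0 time points before treatment and 6 after randomisation. Treatment minus baseline is defined for VAS but not for CMSS.

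**2. Can another entry supply the missing term?**

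- *Procedure section.* For the run-in, participants are told that "they will be asked to record menstrual pain and use of acute medication in a dysmenorrhea diary". CMSS is not named.
- *RSS.* It yields a frequency score and a severity score, whereas CMSS rates severity and duration. Nothing says that RSS provides the CMSS baseline, so subtracting one from the other is undefined.
- *First treatment cycle.* It cannot serve as baseline. Group A starts moxibustion before that period begins, so its first CMSS is already a treated value.

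**3. What the sample size rests on**

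The Sample size section assumes CMSS means of 1.7, 1.9 and 2.5. Their average is 2.033, and their standard deviation is √[(0.333² + 0.133² + 0.467²)/3] = 0.3399. The stated effect size of 0.2266 then implies a within-group SD of 0.3399/0.2266 = 1.50. The effect size is therefore reproduced from CMSS levels in the three groups, not from changes. (The stated power of 90% is not reproduced: 64 per group gives about 80%. That is a separate matter and does not affect this point.)

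**4. What a baseline CMSS would be worth**

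Assumptions, not in the document: equal variance σ² in every cycle and the same correlation ρ between any two cycles (compound symmetry), with ρ from 0.3 to 0.7. The target is the mean of the three treatment cycles. Variances are in units of σ².

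- No baseline covariate: (1 + 2ρ)/3
- One baseline form as covariate: (1 + 2ρ)/3 − ρ²
- Mean of three baseline forms as covariate: (1 + 2ρ)/3 − 3ρ²/(1 + 2ρ)

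| ρ | None | One form | Reduction | Three forms | Reduction |
|---|---|---|---|---|---|
| 0.3 | 0.533 | 0.443 | 17% | 0.365 | 32% |
| 0.5 | 0.667 | 0.417 | 38% | 0.292 | 56% |
| 0.7 | 0.800 | 0.310 | 61% | 0.188 | 77% |

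**5. Covariate or simple change score?**

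With one measurement before and one after, the variance relative to post-treatment values alone is 2(1 − ρ) for a change score: 1.40, 1.00 and 0.60 at ρ = 0.3, 0.5 and 0.7. With the baseline as covariate it is 1 − ρ²: 0.91, 0.75 and 0.51. At 64 per group and effect size 0.2266, omnibus power is 65%, 80% and 96% for change scores and 84%, 91% and 98% with the covariate, against 80% for post-treatment values alone. A raw change score can lose power when ρ is low; the covariate does not.

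**The case against.** **The comparison of groups survives.** The sentence on treatment-minus-baseline differences governs description; the test is in a separate sentence. A repeated-measures analysis of variance can be run on CMSS at visits 2 to 7, the named covariates (age, age at menarche, disease duration) do not include baseline CMSS, and the sample size uses levels. All of this stands. A reader might infer that the primary analysis cannot be run at all, and the document does not support that. What is lost is the stated change and any adjustment for baseline CMSS.

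**The Figure 1 legend points the other way.** It says that "the outcome will be measured at every visit", and visit 1 is a visit. But the legend names no instrument, while the specific text and the CMSS row of Table 2 both leave visit 1 out. It does not supply a baseline, though it should be brought into line. It is also a reason not to assert that no participant actually has a baseline CMSS: the document shows a schedule, not data.

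**The gain may be smaller than it looks.** The 32%, 56% and 77% figures need three baseline forms, so the one-form figures belong to the minimum change. Both sets compare with no baseline covariate. Baseline VAS is already collected and would recover part of the gain, by an amount the document gives no means to estimate.

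**Randomisation protects against bias.** This is correct. Chance imbalance in unmeasured baseline CMSS costs precision; it does not bias the randomised comparison.

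**Conclusion.** The contradiction is real and lies in the primary outcome. The abstract and the Analysis section require a baseline CMSS that the outcome section and Table 2 do not schedule. The stated change cannot be computed from the schedule as written, and baseline CMSS can be neither checked for balance nor adjusted for.

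The consequence is limited. A valid randomised comparison of post-randomisation CMSS levels remains available and matches the basis of the sample size, but it is not the variable the document states.

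The forgone precision is a variance reduction of 17% to 61% with one baseline form, or 32% to 77% with three, over ρ from 0.3 to 0.7. These sizes rest on compound symmetry and an assumed correlation; the contradiction itself depends on neither. The RSS point is minor and is a matter of labelling.

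**What to change.** **Preferred.** In the CMSS section and Table 2, add CMSS to the baseline cycles. The minimum is the last one, completed by visit 1 and before the allocation envelope is opened. Include it as a covariate in the between-group analysis already planned. The repeated-measures test need not be replaced.

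**If baseline CMSS is not added, or some participants were already randomised without it.** Redefine the primary outcome, by dated amendment before analysis, as post-randomisation CMSS compared between groups. Use baseline VAS as covariate, since it is scheduled for everyone; the primary model should use the same covariate for all participants. Recruitment was already open when the article was written, so this case needs to be settled explicitly.

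**In either case.** Bring the abstract, the Analysis section and the Figure 1 legend into line with the choice, and relabel RSS as a baseline measure.

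**Cost.** The preferred change needs one schedule amendment and one to three extra 17-item self-completed forms per participant, in cycles where the diary and VAS are already kept. It needs no extra visits or participants. The alternative needs only the amendment, but gives up adjustment for baseline CMSS itself.
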